## Abstract

**Introduction:**

Patients in intensive care units (ICUs) and their families face existential physical, psychosocial and spiritual distress. Integrating palliative care (PC) into ICU care may benefit patients, relatives and ICU clinicians. Prior PC studies have shown a reduction in ICU length of stay (LOS) and distressing symptoms without altering overall mortality. A shorter ICU LOS may alleviate the burden for patients and relatives and help optimise the use of limited intensive care resources. PC in the ICU, however, remains underused, partly due to limited access and knowledge of ICU clinicians. Also, robust data regarding the effectiveness and cost-effectiveness of PC treatment in the ICU are scarce. We established the ‘enhancing palliative care in ICUs’ (EPIC) study to implement a system-based harmonised practice model across European ICUs. The aim is to investigate if early integration of PC via telemedicine, clinician education and bedside tools is effective and cost-effective, ultimately benefiting patients, relatives and ICU clinicians.

**Methods and analysis:**

This multicentre, controlled, cluster-randomised, non-blinded stepped-wedge design trial with crossover phase aims to recruit around 2,000 patients from five European countries. All adult patients admitted to participating ICUs—with an ICU LOS exceeding 72 hours, where cancer is not the primary cause of critical illness, and who are not expected to die within the next 24 hours—are screened for the need for specialised PC based on the attending physician’s judgement. This judgement is triggered by the presence of one or more of the following: (1) significant disagreement among ICU team members and/or relatives about the appropriateness of current ICU treatment, (2) considerations of limiting life-sustaining therapy or (3) the anticipation that a specialised PC consultation may benefit the patient, their relatives or the ICU team. Patients identified as needing specialised PC and their relatives are then enrolled after obtaining written informed consent.

The complex intervention consists of (a) a blended-learning programme to foster knowledge and attitude about PC among ICU clinicians, (b) bedside tools, including a checklist to identify patients in need of PC and a factsheet and (c) standardised telemedical consultations from trained EPIC interventionists. Patient and relative follow-up is conducted 3 months post-ICU discharge. Outcomes include clinical measures (including ICU LOS (primary outcome), severity of critical illness, invasive treatments and health-related quality of life), economic endpoints (resource use, costs, cost–consequence situation, cost-effectiveness), ICU clinician burnout and distress, and patient and family perception about the quality of symptom management, care and communication. Endpoint analyses will employ generalised linear mixed models, accounting for the clustered data structure and stepped wedge design.

**Ethics and dissemination:**

EPIC complies with the Declaration of Helsinki and has been approved by all local ethics committees. A decision-making structure is established to ensure trial procedures are carried out according to Good Clinical Practice. Study findings will be published in peer-reviewed journals and communicated to participants, healthcare professionals and the public. Sets of anonymised study data will be made available following Findable, Accessible, Interoperable, and Reusable principles.

**Trial registration number:**

NCT06605079.

STRENGTHS AND LIMITATIONS OF THIS STUDYMultinational, multidisciplinary scope: the enhancing palliative care in intensive care units (EPIC) trial is the first European study conducted in multidisciplinary intensive care units (ICUs) across five countries to evaluate a palliative care (PC) intervention, assessing both clinical (such as ICU length of stay, symptom management and health-related quality of life) and economic endpoints, thereby contributing ground-breaking data in several dimensions.Interdisciplinary collaboration: conducted by a consortium of intensive care and PC experts, the pragmatic study fosters collaboration between distinct clinical cultures in real-world settings.Innovative educational and consultative approach: the intervention employs a consultative telemedicine PC model supported by a novel blended-learning programme designed for ICU nurses and physicians, thereby advancing both clinical practice and professional training.Pragmatic comparison with standard care: comparison with standard care across different countries and centres introduces a degree of heterogeneity, but also reflects the real-world complexity of ICU practice and enhances the generalisability of the findings.Patient enrolment affected by ‘subjectivity’: the inclusion criterion ‘need for specialised PC’ based on subjective assessment by the treating physician is partially subjective, reflecting how patients’ needs are assessed in real-world settings and offering an opportunity for clinical practice improvement through the intervention.

## Introduction

 Intensive care units (ICUs) are highly complex and demanding environments. Striking the right balance between technological advances and humane treatment can be challenging. The main focus of ICU care is to prolong a patient’s life, with death being perceived as treatment failure.^1^ ICU mortality varies according to age, comorbidity, critical illness diagnosis and treatment intensity and may reach 80% in specific vulnerable groups (eg, resuscitated cardiac arrest patients).^2^ Providing holistic ICU care without losing sight of the patient’s quality of life and well-being is crucial.

Palliative care (PC) is defined as ‘specialised medical care for people with a serious illness focused on providing relief from the symptoms and stress of the illness’, with the goal to improve the quality of life for both patients and their families.^3^ It can be delivered at two levels: primary and specialised PC. Primary PC, provided by all healthcare providers, mostly focuses on symptom management,^4^ whereas specialised PC is delivered by trained multiprofessional teams in complex clinical situations with an emphasis on holistic support—including symptom control, effective communication, shared treatment decisions and psychosocial patient/family support.^5^

PC specialists can be part of ICU teams in an integrative model but can also advise intensive care physicians in a consultative approach.^6^ This requires an understanding of what PC is in the context of intensive care, as well as when and why it can be useful.^57^,^9^

### Previous findings on PC in the ICU

Several studies have explored PC in the ICU from multiple angles. In addition to work on trigger criteria for identifying patients in need,^10^,^12^ other investigations have evaluated the impact of PC interventions on both patient outcomes and system-based metrics.^6 13^ The literature consistently documents that integrating PC into ICU workflows can reduce ICU length of stay (LOS) without altering overall mortality.^13 14^ A shorter ICU LOS may help optimise the use of expensive and scarce intensive care resources.^15^ However, robust health economic data regarding PC services in the ICU are still limited.^16^

Moreover, early and timely PC in the ICU can:

Address the physical, psychosocial and spiritual suffering of patients and support families and loved ones.Help in prognostic assessment and the establishment of shared therapeutic goals.Enhance collaboration among intensivists, PC physicians, nurses, psychologists and social workers.^8^

Despite these promising findings, PC remains underused in the ICU setting.^17^

### Telemedicine PC

The integration of telemedicine into PC (tele-PC) is defined as the application of telemedicine technologies in the field of PC and presents a promising avenue for addressing the limited local availability of expertise.^18^ Telemedicine may offer an accessible, sustainable and potentially effective approach to deliver PC to ICUs, although evidence—primarily accumulated during the COVID-19 pandemic—remains sparse and randomised controlled trials are lacking.^18^,^20^ Nevertheless, tele-PC may support timely assessments and interventions.^21^

### Rationale of the research project

In light of the substantial burden of morbidity and mortality in the ICU—and the potential added benefits of PC integration via telemedicine—we have established the ‘Enhancing Palliative Care in ICUs’ (EPIC) clinical study. This stepped-wedge trial aims to demonstrate that early integration of PC supporting ICU clinicians by education, bedside tools and the provision of telepalliative care consultations can be achieved through a systems-based approach aligned with a harmonised European care model.

We anticipate that the EPIC study will benefit patients and healthcare staff by optimising care delivery and resource utilisation.

### Objectives and hypotheses

The study will address the following specific objectives:

Clinical outcomes: assess the impact of the complex intervention on ICU LOS, the duration of mechanical ventilation and other organ replacement interventions and the proportion of patients with limitations of life-sustaining therapies.Quality of life: assess the impact of the intervention on health-related quality of life (HRQoL).Economic evaluation: estimate impact on resource use, analyse cost implications and determine the cost-effectiveness and cost–consequence situation of the intervention.Perception of care: evaluate whether patients and their relatives experience improved care quality and communication in the ICU, particularly in relation to end-of-life care and symptom management.Staff well-being: examine whether ICU clinicians (both physicians and nurses) report fewer stressors and perceive an improved ethical decision-making climate and practice.

The primary hypothesis is that the complex intervention will reduce the average ICU LOS by at least 2 days compared with standard care before. Secondary hypotheses include an increase in treatment limitation decisions; improved economic efficiency; enhanced perceived quality of care (notably in symptom management and shared decision-making); an improvement in HRQoL among survivors; and ameliorated moral distress among ICU clinicians.

## Methods

### Overview

We intend to complete a controlled, cluster-randomised, non-blinded stepped-wedge design trial with crossover phase to compare the intervention with standard treatment. Each cluster is formed by all participating ICUs sharing staff within one building or healthcare institution. Standard treatment is provided during the observation phase and the intervention is delivered during the subsequent intervention phase. All ICUs start with the observation phase. All patients who fulfil the eligibility criteria, including the ICU physician’s assessment of the need for specialised PC, are asked to participate in the study. At a randomised time point, each ICU cluster enters a crossover period of 1 month (see online supplemental material figure 1). Within this month, ICU staff receive online training in basic PC and EPIC interventionists are trained to conduct telepalliative consultations. In the subsequent intervention phase, the ICU physicians can use a newly developed checklist to assess specialised PC needs and schedule at least one specialised PC consultation via telemedicine. Survivors’ and relatives’ outcomes are gathered at pre-specified time points, that is, on ICU/hospital discharge and during a 3-month follow-up interview. Clinician outcomes (concerning burnout, end-of-life practices and ethical decision-making) are collected through a dedicated survey scheduled repeatedly in the control and intervention periods. The trial design is illustrated in figure 1.

**Figure 1 F1:**
[figure not shown]
Study overview. Adult patients are screened for eligibility after intensive care unit (ICU) admission. Once enrolled, endpoints/study data are collected retrospectively (ie, for preceding time points as indicated in the grey box) and prospectively (ie, from the time point of enrolment). The enhancing palliative care in ICUs (EPIC) intervention is implemented within the ICU. At discharge, the ICU length of stay is recorded as the primary endpoint, with additional secondary endpoint data concurrently collected. Follow-up occurs at 3 months after ICU discharge and includes questionnaires for both patients and their relatives, along with retrospective collection for the time point of day 28 after ICU discharge.

This trial protocol is presented in accordance with the Standard Protocol Items for Interventional Trials^22^ and also takes into account the Consolidated Standards of Reporting Trials guideline for stepped-wedge cluster randomised trials,^23^ the Standards for Quality Improvement Reporting Excellence guideline^24^ and the Template for Intervention Description and Replication checklist.^25^ Additional details are provided in the online supplemental materials 2–5.

The project’s webpage (https://epic4icu.eu/) provides an overview for clinicians, patients and their relatives.

### Study setting

The study is currently being conducted in seven coordinating clinical centres and numerous multidisciplinary ICUs across five European countries (Czech Republic, Germany, Greece, Israel and Italy). Each coordinating clinical centre is designated as a ‘hub’ providing specialist teleconsultations to remote ICUs, which act as ‘satellites’ where patients are enrolled. The satellite ICUs encompass the full range of intensive care levels.

### Eligibility criteria

Identical enrolment criteria apply for both the observation and intervention phase; therefore, throughout the study period, all consecutive patients who are admitted to a participating ICU will be routinely screened for the following enrolment criteria.

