#### Inclusion criteria

ICU patients with decisional capacity, who can give informed consent for study participation, and incapacitated patients with an available, legally recognised, substitute decision-maker able to provide informed consent on their behalf.Adults aged 18 years and more.The leading cause of critical illness is not cancer; such patients represent a clinically distinct group with different prognosis, pre-existing PC involvement and oncology-specific care pathways that would likely confound the trial’s effect on ICU LOS and other outcomes.^26 27^ Moreover, the most significant evidence gap in the literature on PC for critically ill patients concerns non-cancer populations,^26^,^28^ providing a strong rationale for the inclusion criterion and the design of the present trial.New admission in the participating ICU, with LOS of >72 hours.Need for specialised PC according to attending physician judgement, based on (a) significant disagreement among ICU team members and/or family members about appropriateness of ICU treatment intensity or (b) consideration of therapy limitations or (c) expected benefit from specialised PC consultation for the patient/family and/or ICU team members.

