#### Feedback and support

Feedback loops reinforce protocol adherence, supported by the aforementioned status updates from national coordinators and their associates. Furthermore, at each PC consultation, specialists review screening status, ensuring questionable cases are addressed.

National coordinators continue fostering strong partnerships across all study levels. Identified challenges are resolved through direct communication with clinicians or targeted protocol adjustments. These developments are discussed in three-monthly conference calls of the General Assembly/Executive Board.

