### Sample size calculation

Primary endpoint is ICU LOS in days. We originally planned to recruit 23 ICUs for the trial, each recruiting two to three patients on average per month. Over the trial period of 35 months (including a crossover month without recruitment), we expected each ICU to recruit at least n=87 patients, resulting in at least n=23×87=2001 patients throughout the trial period. Assuming an average ICU LOS of 9 days during the control phase, a sample size of n=2001 patients in the trial would have yielded a power of approximately 85% at a two-sided significance level of 5% to detect a difference in ICU LOS between the intervention and control group of −2 days (SD±9 days).

This calculation was based on simulations using an intracluster correlation coefficient of 0.01 and various possible recruitment schemes with 2–3 average patients recruited per month per ICU. Reducing ICU LOS by 2 days means a clinically relevant reduction of burden by treatment and suffering of patients and their families. The calculations were performed with the software package R (V.4.1.2)^34^ and the programme package swCRTdesign (V.4.0).^35^

During the study initiation phase, 28 ICUs had confirmed participation. To mitigate potential cross-talk between ICUs located within the same institution, we grouped those sharing the same postal address into clusters. As a result, we randomised the crossover time point for each cluster (see online supplemental material figure 1A). Power calculations for this setup indicated an average statistical power of 85% for detecting the expected effect on ICU LOS.

Several months after initiation, two ICUs had dropped out because of delay in contract finalisation or non-recruitment. One ICU was replaced and additional in-house ICU units were added. In July 2025, it was decided to extend the control phase of clusters that had not yet transitioned into the intervention phase by 1 month, without extending the overall study duration of 35 months. This decision was made to mitigate recruitment delays during the control phase and reduce the associated design imbalance between the control and intervention groups. Based on the current recruitment rates and the initial planning assumptions, this modification would conservatively result in a power of approximately 80% at a two-sided significance level of 5% (see online supplemental material figure 1B for the adjusted study design chart).

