#### ICU treatment

Data documented by local research teams for all patients while in ICU include:

Baseline data and critical illness characteristics (date and mode of hospital and ICU admission, ICU admission cause/diagnosis, eligibility criteria, documented pre-existing conditions/medical history, illness severity scores).Symptom burden (psychological, physical, social and spiritual) in the context of specialised PC consultation (intervention period only).HRQoL.ICU clinical course data (complications, organ replacement therapy, highest sequential organ dysfunction assessment score, delirium assessment/duration, treatment limitations).Hospital and ICU discharge data (discharge destination (intermediate care/normal care/death) and date).Patient details (unique identifiers, sociodemographic information, health insurance status).

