#### Data analysis plan

A detailed Statistical Analysis Plan will be finalised before database lock. The analysis of the data will begin with a detailed statistical description of the study sample, differentiated by control and intervention phase. Categorical characteristics will be summarised using absolute and relative frequencies. For ordinal or metric non-normally distributed data with up to five categories, we will present the absolute and relative frequencies, along with the median and the IQR. For data with more than five categories, only the median and IQR will be reported. For metric data that follows a normal distribution, we will present the mean value, accompanied by the SD and the 95% CI.

All analyses will be conducted on an intention-to-treat basis, with the patient representing the unit of analysis. We will use generalised linear mixed models (GLMMs) for continuous outcomes,^23 35^ accounting for the clustered data structure, to compare the primary endpoint between the control and intervention phases. Sensitivity analyses will include additional adjustment for ICU mortality.

Predefined subgroup analyses will be conducted to explore the heterogeneity of the treatment effect in patients concerning sex, religiosity, socioeconomic parameters and educational level. In addition, treatment effects will be compared between ICUs with high-tech versus low-tech telemedicine consultations, with good versus average or poor ethical climate, and ICUs with and without pre-existing palliative counselling. Further comparisons will be made among participating countries, patients with an ICU stay at enrolment of less than 5 days versus at least 5 days, and patients with versus without decisions to limit treatment at enrolment.

Subgroup analyses and analyses of all secondary endpoints will be considered as exploratory. Statistical testing will be carried out at a two-sided significance level of 5%. For the primary hypothesis, no correction for multiple testing is necessary.

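### The intervention acts on the judgement that decides enrolment, so identical written criteria do not ensure comparable patients before and after crossover, and the stated primary model names no case-mix term

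*Protocol article*

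**What the plan says.** Under Eligibility criteria the Protocol article relies on one rule for both phases: "Identical enrolment criteria apply for both the observation and intervention phase", with consecutive screening throughout. The criterion that selects patients is "Need for specialised PC according to attending physician judgement" (Inclusion criteria). It is met by (a) disagreement about treatment intensity, (b) consideration of therapy limitations, or (c) expected benefit from a consultation. The Overview describes a "controlled, cluster-randomised, non-blinded stepped-wedge design trial with crossover phase", so clusters know their phase when they enrol.

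Three elements enter at crossover:

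- PC training of ICU physicians and nurses (Crossover phase).
- The checklist. It is handed out in the crossover month, and the abstract presents it as a means of finding patients who need PC. The Overview says: "In the subsequent intervention phase, the ICU physicians can use a newly developed checklist to assess specialised PC needs".
- Specialist review of screening. Feedback and support says that "at each PC consultation, specialists review screening status, ensuring questionable cases are addressed". Table 8 places the teleconsultation visit in the intervention phase only.

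For the analysis, the Data analysis plan names generalised linear mixed models "accounting for the clustered data structure, to compare the primary endpoint between the control and intervention phases". The abstract adds that the models account for the stepped-wedge design. The one further adjustment named, in sensitivity analyses, is ICU mortality. Baseline data listed under ICU treatment include "ICU admission cause/diagnosis, eligibility criteria, documented pre-existing conditions/medical history, illness severity scores". A detailed SAP is to follow before database lock.

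**The concern.** In a stepped-wedge trial, randomising the crossover times protects the comparison only if the patients who enter the dataset are selected in the same way before and after crossover. Here the selecting criterion is a judgement, the person making it knows the phase, and the intervention is meant to change how PC need is recognised. The wording of the criteria can stay fixed while their application moves.

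Two routes lead to bias in ICU LOS:

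1. **Case mix.** Trained staff with a checklist may enrol patients whom they would not have enrolled before, and those patients may stay for a shorter or longer time.
2. **Time of recognition.** Enrolment is open at any point beyond 72 hours (Table 8), while LOS counts ICU days from the start of the index hospitalisation (Primary outcome). Someone recognised late must still be in the ICU on that later day, so late recognition selects longer stays. Earlier recognition alone can lower mean LOS among enrolled patients, even if no stay is shortened.

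Either route could produce part of the targeted 2-day reduction with no treatment effect, or hide a real one. ICU mortality cannot repair this: it is known only after enrolment, may itself respond to the intervention, and does not measure baseline case mix.

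**Working it through.** **Inputs from Sample size calculation.** 23 ICUs with 87 patients each; 35 months, one of them without recruitment; intracluster correlation 0.01; effect −2 days; SD 9; two-sided 5%; power about 85%, and about 80% after the July 2025 change.

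**Step 1: the plan's own figure.** 23 × 87 = 2001, as stated. Recruitment per ICU-month is 87/34 = 2.56. The check used a linear mixed model with a random cluster intercept, fixed month effects and one empty crossover month per cluster, with power = Φ(2/SE − 1.96). The crossover calendar is in a supplement that is not shown, so evenly spread crossovers were assumed:

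- months 6 to 28 (month index): SE 0.680, power 83.7%;
- months 5 to 29: SE 0.651, power 86.7%.

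Both lie within 2 points of 85%. Other assumed calendars give 65% to 93%. The stated power is therefore reproducible and is taken as given.

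**Step 2: standard error implied by the stated power.** SE = 2/(1.960 + z_power).

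- 85%: 2/(1.960 + 1.036) = 0.667 day.
- 80%: 2/(1.960 + 0.842) = 0.714 day.

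**Step 3: effect of a spurious shift b when the intervention does nothing.** Rejection rate = Φ(−1.96 + b/SE) + Φ(−1.96 − b/SE).

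| Shift b (days) | SE 0.667 | SE 0.714 |
|---|---|---|
| 0.5 | 11.6% | 10.8% |
| 1.0 | 32% | 29% |
| 1.5 | 61% | 56% |

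The nominal rate is 5%. If the shift runs towards longer stay and the true effect is −2 days, power at the 85% design falls to Φ(1.5/0.667 − 1.96) = 61% for 0.5 day and Φ(1.0/0.667 − 1.96) = 32% for 1.0 day.

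**Step 4: could shifts of this size arise?** The article gives no figures, so all inputs here are assumptions.

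*Case mix.* Let f be the share of intervention-phase enrolees who would not have been enrolled under control, and d the difference in their mean LOS. Then b = f × d. With f from 10% to 40% and d from 2 to 5 days, b runs from 0.10 × 2 = 0.2 to 0.40 × 5 = 2.0 days. A middle case is 0.20 × 3 = 0.6 day, which is 30% of the 2-day target.

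*Time of recognition.* Stays were simulated as 3 days plus a log-normal excess with mean 6 and SD 6 or 9, with identical patients in both phases and no effect. Recognition delay beyond 72 hours was exponential, and patients were enrolled only if still in the ICU.

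- Mean delay cut from 4 to 2 days: enrolled mean LOS falls by 0.8 day (SD 6) or 1.2 days (SD 9).
- Mean delay cut from 3 to 2 days: it falls by 0.4 or 0.7 day.

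The 9-day mean in this simulation is that of all stays beyond 72 hours; the enrolled means are higher, at 9.8 to 11.8 days in these runs. The result shows that the mechanism can reach this order of size. It is not a prediction for this trial.

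**The case against.** The strongest reply is that this is a risk and not a demonstrated fault. The attending physician decides in both phases, screening is consecutive, and the checklist is optional. The article admits the subjectivity of the criterion in its strengths and limitations and in the Discussion. It will describe the sample by phase, so a visible difference would come to light. It also predefines subgroups by ICU stay at enrolment (under 5 versus at least 5 days) and by treatment-limitation decisions at enrolment. Finally, a covariate list is normal SAP content, and nothing in the article rules out baseline terms.

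Much of this stands, and it limits what can be said. Four stronger readings are tempting, and the text does not carry them:

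- *That the two phases do compare different patients.* The article contains no data on this, and neither size nor direction can be inferred.
- *That the reported wish to* "mitigate recruitment delays during the control phase and reduce the associated design imbalance" *is evidence of selective enrolment.* That sentence concerns how much recruitment each phase contributes, not who was recruited. It is compatible with a changed enrolment threshold but does not show one.
- *That the model handles clustering and nothing else.* The abstract says it also accounts for the stepped-wedge design.
- *That the missing covariate list is itself the error.* The SAP may supply one. The point rests on the design and on the comparison as stated.

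What does not stand is the protection claimed from identical wording. The stated limitation concerns subjectivity in general; neither place says that the intervention may alter enrolment between phases. The subgroups are exploratory and do not correct selection. Local in-person PC may occur in the control phase, but no matching review of screening is described there.

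**Conclusion.** The concern holds as a built-in risk of selection bias in the primary comparison. The text establishes three things: enrolment turns on an unblinded judgement; training, checklist and specialist screening review act on that judgement only from crossover onward; and the stated primary analysis has no patient-level term that would absorb a resulting difference.

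The size is illustrative. An assumed shift of 0.5 to 1.0 day towards shorter stay would lift the false-positive rate from 5% to about 11% to 32% at the SE implied by 80% to 85% power. The reverse shift would cost a comparable amount of power. These figures rest on the stated power being correct and on assumed shares, LOS differences and recognition delays.

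**What to change.** 1. **Primary model.** Before database lock, pre-specify adjustment for variables fixed at ICU admission and already collected: age, admission SOFA or other severity score, admission diagnosis and mode, and pre-existing conditions. Keep the unadjusted model as a sensitivity analysis. State that this reduces the bias but does not remove it, because unmeasured PC need and time of recognition stay uncorrected. Day of enrolment should be reported but not used as a covariate here, since the intervention may change it. A side benefit, if the covariates explain an assumed 10% of LOS variance: (1.960 + 0.842)/√0.90 = 2.953, so 80% power becomes Φ(2.953 − 1.96) ≈ 84%.
2. **Reporting.** Give screened, eligible and enrolled counts, baseline severity and ICU day of enrolment by phase and cluster. Add the entry criterion met, (a), (b) or (c), where it is recorded; the article lists eligibility criteria as documented but does not say whether the three are stored separately.
3. **Screening review.** Make any review of screening status the same in both phases and do not tie it to PC consultations. The biweekly screening and enrolment reports cannot simply be assumed to fill this role: the article says neither that they run in both phases nor that they examine questionable cases.

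An analysis restricted to criteria (a) and (b) should be exploratory only. The trial hypothesises more treatment-limitation decisions, and (b) is the consideration of such limits, so the intervention may shift (b) as well.

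The cost is SAP wording, one procedural instruction, slightly more analysis work and a somewhat more complex model. Because the trial is already running, item 3 cannot reach patients already enrolled.
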